
### Participant timeline {13}

Table 1 shows the participant timeline.

**Table 1 Tab1:** Participant timeline

**Outpatient Clinic:** Screening (MRI) Study information provided in writing	
**Baseline visit:** Informed consent Baseline study MRI Randomization Baseline PROMs	
Group A: IMPACT	Group B: Control (nonsurgical)
**Preoperative screening** Anti-HLA antibodies	**3 months after inclusion** PROMs Check-up study physician (by telephone)
**Surgery/1 day postoperative** Blood chemistry (CRP, ESR, Leucocytes) Visit physical therapist Check-up rheumatologist Check-up study physician	**6 months after inclusion** PROMs Check-up study physician MRI
**1 week postoperative** Blood chemistry (CRP, ESR, Leucocytes) Check-up rheumatologist Check-up study physician	**9 months after inclusion** PROMs
**4 weeks postoperative** Blood chemistry (CRP, ESR, Leucocytes, anti-HLA antibodies) Check-up rheumatologist Check-up study physician	In case of cross-over to IMPACT: follow group A In case nonsurgical treatment is continued: **12 months after inclusion:** PROMs
**3 months postoperative** Check-up study physician (by telephone) PROMs	**18 months after inclusion:** PROMs MRI
**6 months postoperative** Check-up study physician PROMs MRI	
**9 months postoperative** PROMs	
**12 months postoperative** Check-up study physician PROMs	
**18 months postoperative** Check-up study physician PROMs MRI	

*CRP* C-reactive protein, *ESR* erythrocyte sedimentation rat, *HLA* human leukocyte antigens, *IMPACT* Instant MSC Product accompanying Autologous Chondron Transplantation, *MRI* magnetic resonance imaging; *PROMs* patient-reported outcome measures

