### Criteria for discontinuing or modifying allocated interventions {11b}

Patients can leave the study at any time for any reason if they wish to do so without any consequences. The patient’s participation in this study can also be ended by the investigator if the patient is uncooperative and/or does not attend study visits. The patient data that have been collected up to that moment will be included in the analysis. In case too many data are missing (e.g., missing baseline or all of the follow-up patient-reported outcome measures (PROMs), study visits, or MRI-scans), the patient will be replaced by a new patient. This study will be prematurely ended in case of any abundance in adverse events or procedure/compound-related complications or if the independent rheumatologist advises this termination. Criteria for study termination include any suspected unexpected serious adverse reaction (SUSAR) or serious adverse event (SAE) based on an allergic reaction and clear allergic or iatrogenic effects in two or more patients including patients which report back to the hospital with serious iatrogenic complaints. In case of premature ending, all included patients will be informed by their treating orthopedic surgeon. In case of illness, patients will be asked to contact the primary investigator. Patients that are discovered during surgery not to meet the criteria will not receive IMPACT and will be treated according to the standard of care, based on the findings during surgery. These patients will be removed from the study. Patient data included up to that moment will be included in the analysis.

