### Concealment mechanism {16b}

Allocation is not concealed and will be revealed to both the patient and the researcher upon randomization.

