### Implementation {16c}

After signing the informed consent forms, the researchers will use Castor EDC [26] to allocate the patient to one of the study arms. The study group will be revealed at the same time to both the patient and researcher.

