## Assignment of interventions: blinding

### Who will be blinded {17a}

Patients, researchers, and surgeons will not be blinded, since this is impossible due to the major difference between the two groups (surgical versus nonsurgical).

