### Plans to promote participant retention and complete follow-up {18b}

The patients will receive extensive information about the study set-up and requirements during the recruitment. The importance of completion of the follow-up will be stressed. Patients are allowed to stop at any time during the study and are not obliged to give a reason to discontinue. If possible, the patient will be asked to complete the online survey at 9 months after inclusion. Questionnaires are completed using an online survey, and therefore patients can do this at any convenient moment. All patients are reminded throughout the study to fill out the questionnaires during study visits. Throughout the follow-up period, the researchers will check responses and if necessary contact patients for completion of their follow-up.

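### Table 1 lists randomisation before the baseline questionnaires and nothing requires the reverse, so baseline KOOS may be scored by patients who already know their arm

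*Protocol article*

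**What the plan says.** The order of the baseline visit appears only in Table 1 (Participant timeline {13}): "Informed consent Baseline study MRI Randomization Baseline PROMs".

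The sections on allocation and blinding fit that order:

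- Concealment mechanism {16b}: "Allocation is not concealed and will be revealed to both the patient and the researcher upon randomization".
- Under Implementation {16c}, signed consent is the only step named as coming before allocation. On disclosure, that section says: "The study group will be revealed at the same time to both the patient and researcher".
- Who will be blinded {17a}: "Patients, researchers, and surgeons will not be blinded".

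On questionnaire timing, Plans to promote participant retention {18b} says: "Questionnaires are completed using an online survey, and therefore patients can do this at any convenient moment".

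The primary outcome is total KOOS up to 9 months (Outcomes {12}). The primary model is a mixed model with treatment group and assessment date as fixed factors. Baseline is given as one of the assessment dates, and significance is judged on the treatment-group effect (Statistical methods {20a}).

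**The concern.** A baseline measurement is useful because allocation cannot have affected it. KOOS, NRS and EQ-5D-5L are self-reported, and here the arms are surgery now or at least nine months without it. The Limitations section expects patients to want immediate surgery. It is therefore plausible that relief or disappointment on learning the arm could colour answers given afterwards. The documents do not say that this happens.

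If it did, the arms would differ at baseline for a reason other than chance. Any analysis that uses baseline would carry part of that difference into the estimated effect. This would come on top of open-label reporting at follow-up, which the design cannot avoid. The baseline part can be avoided.

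**Working it through.** **Inputs.** From Sample size {14}: SD 15, correlation 0.7, power 0.8, alpha 0.05, target difference 10, minimum 44, planned total 60. From Trial design {8}: 1:1 allocation. From Objectives {7} and Table 1: visits at 0, 3, 6 and 9 months. Assumed here: equal correlation between all visits, and a baseline arm difference s (IMPACT minus control) of 1 to 5 points in size, caused only by knowing the arm.

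**Step 1: reproduce the 44.** Take the Hotelling-Lawley test of group by time over four visits, with an arm difference of 0 at baseline and 10 at each follow-up.

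- The three changes from baseline have covariance 15² × (1 − 0.7) × (I + J) = 67.5 × (I + J), where J is the 3 × 3 matrix of ones. The inverse is (I − J/4)/67.5.
- Noncentrality = (N/4) × 100 × (3 − 9/4)/67.5 = (N/4) × 1.111. For N = 44 this is 12.22.
- With 3 and 40 degrees of freedom, power is 0.807. At N = 42 it is 0.784. The minimum is therefore 44, as stated.
- Cross-check by normal approximation for change at one visit: variance 225 × 2 × 0.3 = 135, and 2 × 7.849 × 135/100 = 21.2. That rounds up to 22 per arm, 44 in total.

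Other forms give other totals: 72 for one visit without baseline, 38 for one visit with baseline as covariate, and 58 for the mean of three follow-ups without baseline. The form that returns 44 sets the baseline arm difference to zero.

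**Step 2: bias from a baseline difference s.**

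| Analysis | Bias | s = 1 | s = 2 | s = 3 | s = 5 |
|---|---|---|---|---|---|
| Treatment main effect averaged over 4 visits | +s/4 | +0.25 | +0.50 | +0.75 | +1.25 |
| Mean of 3 follow-ups, baseline as covariate | −0.7s | −0.7 | −1.4 | −2.1 | −3.5 |
| Change from baseline | −s | −1 | −2 | −3 | −5 |

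The first row has the opposite sign because baseline is then part of the outcome being averaged. The other two subtract it, wholly or in part. In the first row, a true difference of 10 at three follow-ups and 0 at baseline would itself appear as 30/4 = 7.5.

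**Step 3: effect on the two-sided 0.05 test at N = 60 when there is no true effect.** Type I error = Φ(b − 1.96) + Φ(−b − 1.96), where b = |bias|/SE.

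- Main effect over 4 visits: variance 225 × (1 + 3 × 0.7)/4 = 174.4, SE = √(174.4 × 4/60) = 3.41. At s = 5, b = 1.25/3.41 = 0.37 and type I error is about 0.066.
- Baseline as covariate: variance 225 × [(1 + 2 × 0.7)/3 − 0.49] = 69.75, SE = √(69.75 × 4/60) = 2.16. For s = 1, 2, 3 and 5, type I error is about 0.06, 0.10, 0.16 and 0.37. If s has the sign that shrinks a true effect of 10, power falls from 0.996 to 0.991, 0.979, 0.956 and 0.854.

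**The case against.** The strongest reply is that the sequence is inferred from list order in one table cell, and Table 1 is not consistently chronological. At 3 months and again at 6 months, the questionnaires and the physician check-up appear in opposite orders in the two arms. This stands. It cannot be said that baseline questionnaires are completed after allocation, only that they may be. What remains is that no section requires them earlier.

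Four stronger readings are tempting, and the documents do not support them.

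- A reader might take the freedom to complete surveys at any time as evidence of late completion. It sits in the section on retention and follow-up, and it allows earlier completion just as well.
- A reader might take the replacement rule in Criteria for discontinuing {11b}, which covers "missing baseline or all of the follow-up patient-reported outcome measures (PROMs", as proof that randomised patients can lack a baseline score. The rule does not say that the patient was randomised. It also covers MRI scans, and Table 1 lists the baseline MRI before randomisation. How replacement fits with intention-to-treat is a separate question.
- A reader might apply the largest biases to the primary analysis. Statistical methods {20a} names neither a baseline covariate nor a change-score comparison between arms. The change from baseline in Outcomes {12} is evaluated across all IMPACT-treated patients. For the model as written, s/4 is the relevant figure. Because the sample size reproduces as a group-by-time test, a change-type analysis cannot be ruled out.
- A reader might conclude that the bias could never be removed. A comparison of follow-up scores that leaves baseline out is free of it, at a cost in precision. For the mean of three follow-ups, 2 × 7.849 × 180/100 = 28.3, so 29 per arm and 58 in total, with almost none of the planned 60 left for drop-out.

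It is also fair to say that every follow-up KOOS is already reported with the arm known, so a baseline effect may be the smaller of the two.

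**Conclusion.** The point holds as an avoidable risk, not as a demonstrated bias. Followed as written, the plan lets the baseline of a self-reported primary outcome be scored after the arm is known. The reconstructed sample size takes the baseline arm difference as zero.

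For the primary model as described, the bias is about 0.25 to 1.25 points. It would be 0.7 to 3.5 points with baseline as covariate and 1 to 5 points for change from baseline, against a target of 10. These figures rest on the assumed s of 1 to 5 and on equal correlation of 0.7 between visits. The documents support neither a size nor a direction for s. Because the sign changes with the analysis, the bias cannot be assumed to be conservative.

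**What to change.** - State that baseline KOOS, NRS and EQ-5D-5L must be completed and locked before the randomisation step opens in the EDC system, and reorder the baseline cell of Table 1 to match.
- For patients already included (ten at 15 May 2020, per Trial status), compare questionnaire time stamps with randomisation times and report how many baselines came after allocation.
- Add a sensitivity analysis of the primary outcome that does not use those baselines.

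The sample size stays at 44 minimum and 60 planned. The only cost is that allocation waits for a completed survey. Recruitment was expected to run to about August 2021, so the change would cover up to 50 of the 60 patients if made when the article reported its status.

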**Methods:**

Sixty patients will be randomized to receive nonsurgical care or IMPACT. After 9 months of nonsurgical care, patients in the control group are allowed to receive IMPACT surgery. The Knee Injury and Osteoarthritis Outcome Score (KOOS), pain (numeric rating scale, NRS), and EuroQol five dimensions five levels (EQ5D-5 L) will be used to compare outcomes at baseline and 3, 6, 9, 12, and 18 months after inclusion. Cartilage formation will be assessed at baseline, and 6 and 18 months after inclusion using MRI. An independent rheumatologist will monitor the onset of a potential inflammatory response. (Severe) adverse events will be recorded. Lastly, the difference between IMPACT and nonsurgical care in terms of societal costs will be assessed by monitoring healthcare resource use and productivity losses during the study period. A health economic model will be developed to estimate the incremental cost-effectiveness ratio of IMPACT vs. nonsurgical treatment in terms of costs per quality adjusted life year over a 5-year time horizon.

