### Outcomes {12}

The primary outcome is the comparison in total KOOS between patients with cartilage defects that are treated with IMPACT and patients treated with standard care (nonsurgical treatment) until 9 months after randomization. Total KOOS is an average of the scores in the five subscales of KOOS [23]. Other outcomes of interest are outcomes in the five subscales of KOOS, pain (numeric rating scale, NRS), general health (EuroQol five dimensions five levels, EQ5D-5 L), and structural repair (MRI). After 9 months, patients in the nonsurgical group are allowed to undergo IMPACT surgery, this will be regarded as failed nonsurgical treatment, and the time of crossover will be recorded. Change from baseline assessed with the KOOS of the total group of patients treated with IMPACT at 3, 6, 9, 12 and 18 months after treatment will be evaluated (per protocol). The potential effect of time until surgical treatment will be assessed. Clinical safety will be determined by active tracing of the adverse event rate observed after IMPACT and nonsurgical therapy. Additionally, emergence of an immune response will be assessed by screening for anti-HLA antibodies in peripheral blood preoperatively and 4 weeks postoperatively. The HLA phenotype of MSC donors will be compared to newly formed anti-HLA antibodies. Societal costs will be assessed by monitoring the costs related to the IMPACT procedure and the accompanying rehabilitation period, as well as costs related to nonsurgical (or delayed) treatment. In this analysis, two scenarios will be compared: (I) IMPACT vs. nonsurgical treatment and (II) IMPACT vs. delayed surgical treatment. In the first scenario, it is assumed that patients randomized to nonsurgical treatment will not undergo IMPACT in the next 5 years, whereas the second scenario includes patients who were randomized to nonsurgical care and opt for IMPACT after 9 months follow-up. In both scenarios, costs of other healthcare-related resource use (including physiotherapy, home care, medication use, and costs related to adverse events), as well as costs attributable to health-related work leave (i.e., productivity losses), will be collected over a follow-up period of (at least) 9 months. For nonsurgical treatment, health outcomes (from the EQ-5D-5L) and costs within the first 9 months will be extrapolated to calculate costs/QALY over a 5-year time horizon. Similarly, health outcomes and costs for (delayed) IMPACT will also be extrapolated to a five-year time horizon, using results from the completed phase I/II study (unpublished results).

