### Sample size {14}

The sample size was calculated for the primary objective (treatment effect up to 9 months postoperatively) based on the Hotelling-Lawley trace [24, 25]. Based on a standard deviation of 15 [23], correlation of the repeated measures of 0.7 (data from our phase I trial [21]), and with a power of 0.8 and alpha of 0.05, a minimum of 44 patients should be included to detect a minimal clinical relevant treatment effect of 10 for KOOS [23]. To account for potential loss to follow-up, and uncertainties in the correlation pattern and standard deviation for nonsurgical treatment, this was rounded up to 60 patients in total.

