## Statistical methods

### Statistical methods for primary and secondary outcomes {20a}

Data will be analyzed using IBM SPSS (version 15.0.0.2, Chicago, IL). Data from the primary objective (KOOS, EQ-5D-5L) will be presented as continuous variables. To compare between the two treatment groups, a mixed model analysis will be performed, with treatment group and assessment date of the PROMs (e.g., baseline, 3 months, 6 months) as fixed factors. Differences will be considered statistically significant for the fixed effect of treatment groups if *p* < 0.05 [30]. The 95% confidence interval of the fixed effect size will be used to assess whether treatment difference reaches the minimally clinical important difference.

T1rho-scores will be calculated from the biochemical MRI scans; differences in T1rho-scores will be compared between the time points *t* = 0 (at inclusion before IMPACT or nonsurgical treatment) and *t* = 6 and 18 months after inclusion or surgery. Differences will be compared using Student’s *t* test. The differences in T1rho-score will be tested for normality using Q–Q plots. *P* values less than 0.05 will be considered significant. We will calculate the ICERs of IMPACT vs. nonsurgical treatment and vs. delayed surgical treatment in terms of cost/QALY over a 5-year time horizon. The effect of uncertainty in input parameters on the ICERs will be calculated by means of one-way sensitivity analysis as well as probabilistic sensitivity analyses using Monte Carlo simulation.

All (S)AE(I)s will be summarized and recorded including the nature, date and time of onset, date of resolution, determination of seriousness, severity, action taken, outcome, and possible causality to study treatment. SAE data will be presented in a descriptive manner.

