### Methods in analysis to handle protocol non-adherence and any statistical methods to handle missing data {20c}

The primary outcome will be assessed using an intention-to-treat analysis. Missing data will be reduced to a minimum by using the appropriate measures described above. Mixed models do not require imputations for missing data. If any statistical method is needed to account for missing data in the secondary outcomes, multiple imputation will be used.

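### The primary KOOS has two time origins in the IMPACT arm, randomisation in the outcome definition and surgery in the visit schedule, so the arms are misaligned if Table 1 is followed

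*Protocol article*

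**What the plan says.** Four places in the protocol article give a time origin for the primary KOOS.

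- Outcomes {12}: the arms are compared "until 9 months after randomization".
- Abstract, Methods: the patient-reported measures "will be used to compare outcomes at baseline and 3, 6, 9, 12, and 18 months after inclusion", with no distinction between arms.
- Participant timeline {13}, Table 1: the last primary visit of the IMPACT arm is "9 months postoperative" and that of the control arm is "9 months after inclusion". The 3- and 6-month visits follow the same pattern.
- Sample size {14}: the trial is sized for the "treatment effect up to 9 months postoperatively".

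Table 1 places consent, randomisation and baseline questionnaires at one visit, followed in the IMPACT arm by preoperative screening and then surgery. The primary analysis is a mixed model "with treatment group and assessment date of the PROMs (e.g., baseline, 3 months, 6 months) as fixed factors". On the population, the plan states: "The primary outcome will be assessed using an intention-to-treat analysis". The retention section {18b} adds that patients who stop will, where possible, be asked for one online survey nine months from inclusion.

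**The concern.** The first two places start the clock at randomisation or inclusion in both arms. The last two start it at surgery in the IMPACT arm. Both cannot hold unless surgery falls on the day of randomisation, and Table 1 puts a screening step in between.

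The visit factor in the primary model takes nominal labels. Under Table 1 the label for month 9 marks nine months from randomisation in controls and a later, variable time in the IMPACT arm. An intention-to-treat comparison starts at randomisation and includes any wait that allocation brings. Table 1 as written would not deliver that comparison, although Outcomes {12} and the analysis population statement promise it.

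Recovery is still in progress over this window. The intervention section has patients reaching full weight-bearing at 8 to 12 weeks, working on strength and function from 5 months, and returning to low-impact sport only after 9 months. A shift in assessment time can therefore plausibly change the score. A questionnaire that was not sent on the right date cannot be recovered at analysis, so a later analysis plan could not fully repair this.

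**Working it through.** **1. The plan's own figure.** Inputs from Sample size {14}: SD 15, correlation 0.7, difference 10, power 0.8, alpha 0.05; allocation is 1:1. Assumptions for the check: compound symmetry; occasions at baseline, 3, 6 and 9 months; a difference of 0 at baseline and 10 at each follow-up.

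- The covariance of the three changes from baseline is 15² × (1 − 0.7) × (I + J) = 67.5 (I + J), with I the identity and J the all-ones matrix.
- Since (I + J)⁻¹ = I − J/4, the noncentrality is λ = (N/4) × 100 × (3 − 9/4) / 67.5 = (N/4) × 75/67.5.
- At N = 44, λ = 11 × 1.111 = 12.2 on 3 and 40 degrees of freedom, giving power 0.807. At N = 60 power is 0.927.

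The stated 44 is reproduced. The calculation contains no calendar time, so the choice of origin does not alter it; what may change is whether 10 points is the effect seen at the chosen times.

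**2. Displacement under Table 1.** Let L be the months from randomisation to surgery. The document does not give L, so the values below are assumptions. An IMPACT visit labelled month m takes place m + L months after randomisation; the control visit takes place at m. The gap is L at every visit and is zero only if L = 0.

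| Assumed L (months) | IMPACT visits, months after randomisation | Control visits | Months since surgery if IMPACT were assessed 9 months after randomisation (9 − L) |
|---|---|---|---|
| 0 | 3, 6, 9 | 3, 6, 9 | 9 |
| 1 | 4, 7, 10 | 3, 6, 9 | 8 |
| 2 | 5, 8, 11 | 3, 6, 9 | 7 |
| 3 | 6, 9, 12 | 3, 6, 9 | 6 |
| 6 | 9, 12, 15 | 3, 6, 9 | 3 |

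Between the baseline questionnaire and 3 months after surgery, Table 1 schedules no KOOS in the IMPACT arm.

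**3. IMPACT patients who are never operated on.** Without a surgery date, Table 1 gives no date for any follow-up questionnaire. The retention section supplies one attempt, nine months from inclusion, and nothing at 3 or 6 months. Within the IMPACT arm, that score would stand at 9 months after randomisation and those of operated patients at 9 + L, under the same label.

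**4. Room for a smaller effect.** The noncentrality is proportional to N × difference². At N = 60 the difference giving the same 12.2 is 10 × √(44/60) = 8.6 points, for the same flat profile and all 60 analysed. The increase from 44 to 60 is, however, already meant to cover loss to follow-up and uncertainty in the correlation and SD.

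**The case against.** The strongest reply is that timing by treatment start looks deliberate. The statistical methods section times MRI from inclusion or surgery, the sample size section counts from surgery, and Table 1 sends crossover patients through the IMPACT schedule. Comparing arms at equal time since treatment began is an intelligible question. This stands as an account of how Table 1 arose, and it means Table 1 cannot be taken as the only operative rule. It does not remove the conflict: Outcomes {12} names randomisation for the primary comparison and describes separately a per-protocol analysis timed from treatment.

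The wait may also be short. The data monitoring section expects rapid inclusion and treatment. It gives no interval, so L could be small, but it is not shown to be.

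Three stronger readings are tempting and are not supported.

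- A reader might infer that unoperated IMPACT patients have no assessment at all and that intention-to-treat is impossible. The retention section provides a best-effort 9-month survey, baseline scores are collected at the randomisation visit, and a mixed model uses whatever is available. Intention-to-treat is weakened, not ruled out.
- A reader might count patients found ineligible at surgery among those without a date. They do have an operation date. They lose follow-up because the discontinuation section {11b} removes them from the study, which is a separate matter that re-timing would not cure.
- A reader might put a size on the bias. An assumed wait of 1 to 3 months times an assumed slope of 1 to 2 KOOS points per month gives 1 to 6 points, but neither factor has any basis in the document.

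Nor is the wait wholly left out of the IMPACT result. Baseline precedes it, so any net change over the wait carries into change from baseline. What is missing is a measurement during it.

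**Conclusion.** The point holds as an internal contradiction over the timing of the primary endpoint. The abstract and Outcomes {12} use inclusion or randomisation; Table 1 and Sample size {14} use surgery for the IMPACT arm. If Table 1 is followed, IMPACT assessments fall L months later after randomisation than the control assessments they are paired with, and the visit factor is misaligned between arms. The intention-to-treat outcome as defined is then not what is measured.

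That conclusion needs only that surgery does not occur on the day of randomisation. The size and direction of any bias in KOOS points depend on L and on the recovery course, and the document gives no figure for either. If scores are still rising around month 9, the later assessment would favour IMPACT, but this is conditional. The stated minimum of 44 patients is unaffected.

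**What to change.** Name randomisation as the single time origin for the primary KOOS at 3, 6 and 9 months in both arms, and state that this includes IMPACT patients who are not operated on. Collect these scores through the existing online survey. Amend Table 1 and Sample size {14} to agree with Outcomes {12}. Keep the postoperative questionnaires for the per-protocol change-from-baseline analysis of all patients treated with IMPACT.

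For patients already included (ten by 15 May 2020), report the actual time from randomisation to each assessment and use it in a sensitivity analysis.

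The cost is up to three extra online questionnaires per IMPACT patient, at most 3 × 30 = 90 with 60 patients allocated 1:1, plus an amendment to the table and text. There is also a statistical price: IMPACT patients would be assessed 3 − L, 6 − L and 9 − L months after surgery, hence earlier in recovery, and at 3 months possibly before surgery if L exceeds 3. The observed effect, and with it the power against 10 points, may be lower. The sample size section should acknowledge this when it is re-worded.
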